## Methods

### Aim

The main aim of this prospective study is to investigate the impact of the COVID-19 pandemic on perinatal mental health (depression, anxiety, and post-traumatic stress symptoms).

The primary objectives are the following:
To evaluate changes in perinatal mental health outcomes (symptoms and indices of clinical risk for mental disorders) during the COVID-19 pandemic.

We will evaluate the changes in (a) perinatal mental health symptoms (depression, anxiety and post-traumatic stress disorder [PTSD]); and (b) clinical risk indices (proportion of women above the clinical cut-off point on a validated self-report scale) for depression and anxiety disorders. We will compare the results to similar pre-pandemic studies in all the countries. We will also assess the acute and long-term mental health impact of different phases of the COVID-19 pandemic by measuring the changes in perinatal mental health outcomes between the initial survey and the follow-up assessments.
2)To determine the risk and protective factors that predict perinatal mental health outcomes during the COVID-19 pandemic.

We will determine the risk and protective factors that predict PTSD symptoms and the clinical risk of depression and anxiety disorders (proportion of new cases above the cut-off point on validated self-report scales in the follow-up period) during the COVID-19 pandemic. Factors included in our study were based on recent literature [24–28] and include demographic variables, COVID-19 epidemiology and public health measures, perinatal experiences during the COVID-19 pandemic, and psychological distress.

Furthermore, additional secondary objectives related to the impact of COVID-19 on perinatal mental health will also be examined: the comparison of perinatal mental health outcomes between the countries participating in the study; breastfeeding and its protective role in perinatal mental disorders; the risk of perinatal mental disorders in COVID-19-positive women vs. COVID-19-non-positive women; and factors associated with the level of distress of women during the perinatal period.

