### Study design

This is an international prospective observational cohort study, with a baseline and three follow-up assessments: at one, three, and six months post-baseline. The observation period will be 6 months, from the initial evaluation to the last follow-up assessment. The overall study will span from 15 June 2020 to 15 June 2021.

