### Participants

The study population consists of women during the perinatal period. The rationale is to evaluate women throughout their pregnancy and during 1 year after childbirth, for a six-month period (from baseline to follow-up). Women can, thus, enter the study during pregnancy or at any time during the first 6 months following childbirth [29].

The inclusion criteria at baseline are:
Being pregnant or a biological mother of a child six months of age or youngerWomen 18 years of age or olderLiving in one of the countries involved in the studyConsenting to participate in the study

The exclusion criteria are:
Not being currently pregnant or not being the biological mother of a child six months of age or youngerWomen younger than 18 years of ageLiving in a country that does not participate in the study.Not consenting to participate in the study

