### Data analysis

Patterns of missingness in the data will be studied and the Expectation-Maximization algorithm will be implemented to impute missing data. Attrition analyses will be carried out to examine differences between participants who completed all the assessments and those who did not. Descriptive statistics will be examined for the study variables for all the assessment times. Measurement equivalence will be studied in order to ensure we are measuring the same variables across countries.

Changes in mental health between baseline and the follow-ups will be examined by testing latent growth curve models for each outcome. Moreover, the relationships between the rates of change in predictors (i.e., risk and protective factors) and mental health results during the follow-up will be analyzed. Multilevel analyses will be performed to control the moderation of demographic variables in those interrelations. Regarding the overall fit of these models, Satorra-Bentler χ^2^, CFI, RMSEA and the confidence interval for the RMSEA statistics will be calculated. Lagrange multipliers and the Wald test will be performed sequentially to improve the fitness of the models, following the hypotheses of the study. Standardized coefficients and measurement equations with scores in R^2^ will be reported. These analyses will be undertaken using the statistical program EQS. 6.3.

To determine the risk and protective factors to predict perinatal mental health outcomes during the COVID-19 pandemic, a random sample of 70% of the data will be used to derive the machine learning algorithms including regularized logistic regression, random forest, decision tree, and gradient boosting to predict the risk of PPD, and their performance, and the remaining 30% for validation. First, in the derivation sample, all the predictors described above will be entered into the models to estimate the probability of depression or anxiety or PTSD. Beginning with a model containing all potential covariates, the variable with the least significant *P* value will be removed and tested using the likelihood-ratio test until all variables left in the model significantly (at alpha = 0.05) contribute to the model.

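### The baseline-to-follow-up change in objective 1 is read as the impact of pandemic phases, but the growth models name no term for perinatal stage and do not tie the dated OxCGRT data to that change

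*Protocol article*

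**What the plan says.** Under Aim, the protocol undertakes to "assess the acute and long-term mental health impact of different phases of the COVID-19 pandemic by measuring the changes in perinatal mental health outcomes", specifically the change from the initial survey to the follow-ups. The Data analysis section carries this out: "Changes in mental health between baseline and the follow-ups will be examined by testing latent growth curve models for each outcome". It adds an analysis relating rates of change in predictors to the outcomes, and multilevel analyses that adjust for demographic variables.

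Three design facts bear on this:

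- **Timing of waves (Study design):** follow-ups fall "at one, three, and six months post-baseline".
- **Calendar window (Study design):** "The overall study will span from 15 June 2020 to 15 June 2021".
- **Entry (Participants):** "Women can, thus, enter the study during pregnancy or at any time during the first 6 months following childbirth".

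Two other elements are relevant. OxCGRT data are taken by assessment date and listed in Table 1 as a predictor at baseline and all three follow-ups. Objective 1 also promises a comparison with similar pre-pandemic studies, which is a separate route to a pandemic effect.

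**The concern.** Change over survey waves is given a pandemic interpretation, yet three clocks advance together for each woman: time since her baseline, calendar date and perinatal stage. The Background section itself describes the perinatal period as one of raised vulnerability to mental disorder, so a stage effect on EPDS, GAD-7 or PTSD scores cannot be assumed to be nil. The longitudinal models name no term for gestational or postpartum time, and the items under Demographics include neither.

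If the plan is followed as written, a rise or fall that comes from women moving through pregnancy, birth and the postpartum months could be credited to the pandemic. Opposing stage and phase effects could also cancel and be reported as no change. Either would affect a primary objective.

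**Working it through.** The plan gives no figure for this quantity, so there is nothing to reproduce. The check is structural, followed by illustrations on assumed effects.

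**1. Spread of the clocks (from the documents).** Six months of follow-up ending by 15 June 2021 puts the latest fully followed baseline at about 15 December 2020, 183 days after 15 June 2020. At that limit, one woman's baseline falls on the date of another's six-month survey. This is an outer bound, because no enrolment dates are given. Perinatal stage at entry can span about 9 + 6 = 15 months. At the six-month survey it can run from about 3 months before birth to 12 months after.

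**2. What a wave slope estimates.** Take a woman entering at calendar time e and stage g, with linear trends p (pandemic) and s (stage) per month. At t months after baseline,

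score = a + p(e + t) + s(g + t),

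so her slope in t is p + s. Waves alone cannot separate the two.

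**3. Simulation.** 14 countries × 300 = 4,200 women were surveyed at 0, 1, 3 and 6 months. Assumed: entry uniform over six months, stage at entry uniform from 8 months before to 6 months after birth, between-woman SD 4, residual SD 3, no dropout. Units are points per month.

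| True pandemic trend | True stage trend | Wave slope |
|---|---|---|
| 0 | −0.2 | −0.195 |
| −0.2 | 0 | −0.208 |
| +0.2 | −0.2 | −0.006 |

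The first two rows cannot be told apart, and in the third both effects vanish. With no stage effect and one assumed pandemic peak in mid-January 2021, the wave slope was +0.32 when all women entered in the first six weeks or so of the window, +0.09 with uniform entry and −0.22 with entry in the last six weeks or so.

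**4. Does a stage-and-calendar model separate them?** A random-intercept model with calendar month and perinatal stage in place of wave gave, for the three rows in order:

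| True pandemic, stage | Estimated pandemic | Estimated stage |
|---|---|---|
| 0, −0.2 | 0.006 | −0.209 |
| −0.2, 0 | −0.185 | −0.013 |
| +0.2, −0.2 | 0.211 | −0.202 |

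Standard errors were about 0.017 (pandemic) and 0.015 (stage). The separation comes from differences between women in entry date and stage, and the simulated data contained no entry-cohort effect.

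**5. Illustrative size on the EPDS (all inputs assumed).** Half the cohort is pregnant at entry, with gestation uniform over weeks 6 to 40. Women beyond week 40 − 26 = 14 deliver within 26 weeks: (40 − 14)/(40 − 6) = 0.76. Share of the cohort changing stage: 0.5 × 0.76 = 0.38. Shift in mean = 0.38 × stage difference:

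- 0.5 points: 0.19
- 1 point: 0.38
- 2 points: 0.76

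With SD 5.5, wave correlation 0.6 and 40% retention of 4,200 (1,680 women), the standard error of the mean change is 5.5 × √(2 × 0.4)/√1,680 = 0.120. The z values are then about 1.6, 3.2 and 6.3.

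**The case against.** The strongest reply has several parts.

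- **The time score is not named.** A reader might infer that the growth curves certainly run on survey wave. The article does not say so, and individually dated times would be compatible with its wording. Time coding is also commonly left to an analysis plan. This stands as a caution. It does not remove the point, because the Aim section itself equates survey-to-survey change with phase impact.
- **Pandemic phase is partly covered.** Dated OxCGRT values are planned predictors at all four assessments and could enter the rates-of-change analysis. This stands, so it would be wrong to say that phase is ignored. The text does not, however, tie these values to the estimated change, and they do nothing for perinatal stage.
- **Objective 1 does not rest on this alone.** A reader might conclude that its whole answer is uninterpretable. The documents do not support that, because the pre-pandemic comparison is a separate route.
- **Entry may have been concentrated.** Baselines running from June to mid-December are only what the outer dates allow, and the Discussion mentions a need to obtain a sample rapidly. With concentrated entry, wave and calendar date would largely coincide. The mixing with perinatal stage would remain.
- **Regression to the mean.** It might be added as a further source of change, but no symptom threshold applies at entry and self-selection is already declared as a limitation. It is not relied on here.
- **Size.** The inputs are assumptions. At the low end the shift would not reach significance, and 0.38 points is about 0.07 SD (0.38/5.5).

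**Conclusion.** The concern holds for the baseline-to-follow-up part of objective 1. This is more than an omitted detail: the protocol states the inference from change to pandemic phase, and its named adjustment cannot support it when entry spans pregnancy to six months postpartum. Perinatal stage is the firm part of the finding. The phase part is narrower: the data are planned, but their link to the estimated change is not stated.

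That a wave slope mixes the two follows from the design and needs no numerical assumption beyond a non-zero stage effect. Its size cannot be established from the documents. The 0.19 to 0.76 EPDS points and the simulated slopes only show what could happen under the stated assumptions.

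**What to change.** In the objective 1 growth models:

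- Add time-varying perinatal stage: gestational weeks before birth and postpartum weeks after it, with a term for the birth transition.
- Add the already planned date-linked OxCGRT values, or calendar period.
- Let pregnant and postpartum entrants have their own intercepts and slopes.
- Base any pandemic-phase conclusion on the OxCGRT or calendar term, and call the wave slope descriptive.
- State that linear stage and calendar effects are separated mainly by differences between women in entry date and stage, which assumes no entry-cohort effect.
- Add months since baseline only as a sensitivity analysis, since it advances together with the other two clocks within a woman.

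Use infant birth dates or due dates if they are already recorded. The growth models are assigned to EQS, and R is named only for the prediction models, so amend the software sentence if EQS cannot fit this specification.

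The cost is more parameters, wider intervals and some extra analysis work.

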We hypothesize an increase in negative perinatal mental health outcomes (symptoms and clinical risk) among women during the COVID-19 pandemic. We also hypothesize that common risk factors (e.g., low income, low social support, high level of psychological distress, previous history of mental disorders) will be associated with an increase in the clinical risk of depression and anxiety during the COVID-19 pandemic. Additionally, we hypothesize that pandemic-related risk factors, such as being exposed to and/or having a positive diagnosis for COVID-19, will be associated with increased risk of perinatal mental disorders.

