### Variables and measures

The variables and measures planned for the different phases of the study are presented in Table 1.

**Table 1 Tab1:** Variables and measures used in each phase of the study

Variables	Measures	Baseline	T1	T2	T3
*Independent/predictor*					
COVID-19 epidemiology and public health measures	OxCGRT	X	X	X	X
Demographic variables	14 questions	X			
Perinatal health care experiences related with COVID-19	COPE-IS	X			
COVID-19 exposures and symptoms	COPE-IS; COPE-IU	X	X	X	X
COVID-19 financial impact	COPE-IS; COPE-CF	X	X	X	X
COVID-19 social support impact	COPE IS; COPE-CF	X	X	X	X
COVID-19 coping strategies	COPE-IS; COPE-IU	X	X	X	X
COVID-19 emotional impact	COPE-IS; COPE-IU	X	X	X	X
Health background, mental health, and substance use	COPE-IS	X			
Psychological distress	BSI-18	X	X	X	X
*Dependent/outcome*					
Depression symptoms	EPDS	X	X	X	X
Anxiety symptoms	GAD-7	X	X	X	X
PTSD symptoms	10 questions from PTSD Checklist for DSM-5 included in COPE-IS; COPE-IU	X	X	X	X

T1: 1-month follow-up; T2: 3-month follow-up; T3: 6-month follow-up; PTSD: Post-traumatic Stress Disorder; OxCGRT: Oxford COVID-19 Government Response Tracker; COPE-IS: Coronavirus Perinatal Experiences - Impact Survey; COPE-IU: Coronavirus Perinatal Experiences Scale - Impact Update; COPE-CF: Coronavirus Perinatal Experiences Scale - Care Follow Up; BSI-18: Brief Symptom Inventory-18; EPDS: Edinburgh Postnatal Depression Scale; GAD-7: Generalized Anxiety Disorder Screener

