#### Demographics

This questionnaire will include a subset of 14 questions about the women’s date and country of birth; state/city of residence; educational level; number of previous pregnancies; number of biological children (including stillbirths); number of people living at home (adults and children); marital status; cohabitation with partner; characteristics of the home (inside and outside spaces in square meters); and living environment changes since the beginning of the pandemic.

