##### Physical and mental health history and substance use

Thirteen items addressing: 1) the women’s and family (partner, child or other members of the household) history of the following medical conditions: respiratory problems, diabetes, heart disease or hypertension, lung disease; liver disease; cancer; disease compromising the immune system; mood and/or anxiety disorders; 2) whether currently receiving treatment for mental disorders (for example, depression, anxiety, stress, ADHD, bipolar disorder, eating disorder or PTSD); 3) current substance use; and 4) current treatment of medical conditions [31].

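### The growth-model associations name only demographic variables as controlled, so baseline mental disorder history and current treatment, already collected, may confound them

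*Protocol article*

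**What the plan says.** The Data analysis section of the protocol article plans a latent growth curve model for each outcome. It then adds that "the relationships between the rates of change in predictors (i.e., risk and protective factors) and mental health results during the follow-up will be analyzed". The next sentence is the only one that names variables to be controlled in these associations: "Multilevel analyses will be performed to control the moderation of demographic variables in those interrelations".

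Three other places bear on what that sentence covers:

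- **Demographics.** The set is defined by its content: "This questionnaire will include a subset of 14 questions about the women’s date and country of birth; state/city of residence; educational level", followed by pregnancies and children, household, marital status and features of the home. None of the listed topics is mental health history.
- **Physical and mental health history and substance use.** The baseline COPE-IS asks about history of "mood and/or anxiety disorders; 2) whether currently receiving treatment for mental disorders". Table 1 marks the row "Health background, mental health, and substance use" at baseline and at no follow-up.
- **Aim.** The hypotheses include "previous history of mental disorders" among the common risk factors, in the same list as low social support.

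**The concern.** A woman's psychiatric history can affect how her symptoms develop over six months. It can also affect how her social support, coping, finances and stress develop. If it does both, a model that relates the two courses without adjusting for history will show an association even where neither acts on the other. Support or coping would then be credited with part of what belongs to history. This matters because the article intends to specify the contribution of each risk and protective factor and to use the results in designing interventions.

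Relating changes to changes does not remove the problem. It cancels a fixed trait's constant effect on level, but not an effect on the trajectory. If the mental health results are analysed as levels during follow-up, the effect of history on level matters as well.

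The wording of the control sentence is a second difficulty. Moderation is something to estimate, through an interaction or a comparison of groups. Saying that it will be controlled leaves open whether any variable, demographic or other, is entered as a confounder.

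**Working it through.** The plan gives no figure for this analysis, so there is none to reproduce. The check has a textual part and an illustration of size.

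**1. Can history enter by a route the text states?** The growth associations have two stated entry points.

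- As a rate of change in a predictor: no. Table 1 shows one measurement, at baseline, and a variable measured once has no rate of change.
- As a demographic variable: no. The topics listed for the 14 demographic questions do not include it.

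No other sentence adds it as a covariate of the growth models.

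**2. Is it covered elsewhere?** Yes, for another analysis. The prediction models for objective 2 start from all predictors, which in Table 1 include mental health background. Backward removal at alpha 0.05 may later drop it. Those models estimate the probability of an outcome and do not adjust the growth associations.

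**3. How large could the bias be?** Let a share p of women have a history, let history shift both the predictor slope and the outcome slope by d within-group SDs, and let there be no other link between the slopes. Then

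r = d²p(1−p) / [1 + d²p(1−p)], and approximately z = r√n.

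Inputs:

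- p = 0.2, assumed. The Background's 1 in 5 is the share of women who develop a disorder in the perinatal period, not the share with a prior history, so it does not supply this value.
- d = 0.2, 0.5 and 0.8, assumed. The documents give no value.
- n = 14 countries × 300 (Setting; Sample size) = 4,200. n = 2,100 assumes that half remain.

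With p(1−p) = 0.16:

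| d | d² × 0.16 | r | z, n = 2,100 | z, n = 4,200 |
|---|---|---|---|---|
| 0.2 | 0.0064 | 0.0064/1.0064 = 0.006 | 0.3 | 0.4 |
| 0.5 | 0.0400 | 0.0400/1.0400 = 0.038 | 1.8 | 2.5 |
| 0.8 | 0.1024 | 0.1024/1.1024 = 0.093 | 4.3 | 6.0 |

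Against 1.96, the smallest effect is negligible at either size. The middle one crosses only at 4,200, and the largest crosses at both.

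**4. A second parametrisation.** If history correlates a with the predictor slope and b with the outcome slope, the spurious correlation is a × b. For a and b each from 0.1 to 0.4 (assumed), it runs from 0.01 to 0.16. By the Fisher z approximation at two-sided 0.05, the chance of declaring an association when there is no direct link is:

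| a = b | a × b | n = 300 (one country) | n = 4,200 |
|---|---|---|---|
| 0.1 | 0.01 | 5% | 10% |
| 0.2 | 0.04 | 11% | 74% |
| 0.3 | 0.09 | 34% | near 100% |

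Both calculations treat slopes as observed without error. Slopes estimated from four assessments are less precise, so the z values and rejection rates are on the high side.

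**The case against.** The strongest reply is that the text does not exclude other covariates. It addresses moderation by demographics and does not present this as the full adjustment set, and an article may leave a full covariate list to the complete protocol or SAP. The text also calls predictors risk and protective factors, Table 1 lists mental health background among them, and a baseline variable can enter a growth model as a time-invariant covariate. This stands as far as it goes: history is not ruled out, and a missing list would be no finding. What remains is that the article does state a control, states it in terms that do not describe confounder adjustment, and leaves a named risk factor outside it.

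A reader might infer that history is definitely excluded and does confound the results. The documents do not support that. Confounding requires history to be related both to change in the predictor and to the outcome, and they give no values for either.

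A reader might also infer that the whole risk-factor objective is affected. It is not, since the objective 2 prediction models enter history.

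Nor does the choice of a multilevel model amount to an error. Such a model can carry woman-level covariates and can estimate moderation through cross-level interactions. The structure alone does neither unless those terms are specified.

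Finally, the assumed effects may be too large. History may act more on symptom level than on six-month slopes, and at d = 0.2 the bias is negligible. That is why the size is given as a range.

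**Conclusion.** The point holds in limited form. In the growth and multilevel models, demographic variables are the only ones named as controlled, and the wording concerns moderation. History of mood or anxiety disorder and current treatment are measured and lie outside both the demographic set and the rate-of-change predictors; history is also a hypothesised risk factor. They may confound these associations.

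The spurious slope correlation is about 0.006 to 0.09 with 20% prevalence and shifts of 0.2 to 0.8 SD on both slopes, all assumed. Whether the bias is trivial or material cannot be settled from the documents. This is an inexpensive improvement to one part of the analysis and does not undermine the study as a whole.

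**What to change.** In the growth and multilevel models, include the woman's own baseline history of mood or anxiety disorder and her current treatment for mental disorders, together with the demographic variables, as time-invariant (woman-level) covariates of the intercepts and slopes of both predictor and outcome. Her own history must be separated from that of her household, because the COPE-IS item covers both.

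Replace the phrase about controlling moderation with a statement that demographic moderation will be estimated through interactions or multi-group models and reported. The multilevel framework can stay.

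The cost is a change of analysis wording and a few more parameters per model. The variables are already collected at baseline.

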In regularized logistic regression models, results will be presented as odds ratio (OR) with 95% confidence intervals (CIs). The R^2^ will be used to calculate the proportion of the explained variance of clinical outcomes by the selected predictors. The different aspects of model performance will be studied, including calibration and discrimination. Calibration will be assessed using the Brier score and by plotting the non-parametric estimate of the association between the observed frequencies and the predicted probabilities. The receiver operating characteristic (ROC) curves (and the corresponding area under the ROC curve—AUC) will be calculated to test for discrimination. To correct optimism, internal validation will be performed for each model using the bootstrap procedure with 500 bootstrapped samples. The final models will be selected to derive scores for clinical use, and nomograms will be created. Criteria for this selection will include both discriminant ability (defined by the AUC) and model simplicity. Finally, the coefficients (scores) derived from the derivation cohort will also be validated in the validation cohort. These statistical analyses will be carried out in R and Python. The analyses will conform to the reporting standards of transparent reporting of a multivariable prediction model for individual prognosis or diagnosis (TRIPOD) [49].

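### The growth models are respecified by sequential Lagrange-multiplier and Wald tests with no hold-out or optimism correction, so fit will tend to be overstated and chance predictor paths can enter

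*Protocol article*

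**What the plan says.** All of this stands in the protocol's Data analysis section, except for the hypotheses, which are in the Aim section.

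- Growth models: "Changes in mental health between baseline and the follow-ups will be examined by testing latent growth curve models for each outcome". Links between change in predictors and change in outcomes are analysed in the same block.
- Fit: "Satorra-Bentler χ^2^, CFI, RMSEA and the confidence interval for the RMSEA statistics will be calculated".
- Respecification: "Lagrange multipliers and the Wald test will be performed sequentially to improve the fitness of the models, following the hypotheses of the study".
- Reporting: "Standardized coefficients and measurement equations with scores in R^2^ will be reported".
- Software for this block: "These analyses will be undertaken using the statistical program EQS. 6.3".

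The safeguards come later, in the prediction block. There "a random sample of 70% of the data will be used to derive the machine learning algorithms", with the other 30% kept for validation. To correct optimism, "internal validation will be performed for each model using the bootstrap procedure with 500 bootstrapped samples". That block closes with "These statistical analyses will be carried out in R and Python".

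The Aim section hypothesises worse outcomes during the pandemic and associations with risk factors. It names four common factors and two pandemic-related ones, in both cases as examples and not as a closed list.

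**The concern.** A Lagrange-multiplier test picks the parameter whose release most improves fit, and a Wald test picks the one whose removal costs least. Applied in sequence, they make a specification search. Chi-square, CFI, RMSEA, p-values and R² have their usual meaning only for a model fixed before the data were seen. After a search they describe a model that the same data chose.

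Two results are at stake. One is the fit statistics, which readers will use to judge whether the growth models are adequate. The other is the set of associations between predictors and change, where a path that entered because it passed a test will look stronger than it is. The authors recognise optimism and correct for it in the prediction block, but attach no such step here.

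**Working it through.** **The plan's own figures.** The protocol gives no number for this procedure: no entry or removal level, no list of candidate paths and no stopping rule. Its only sample-size figure is 300 per country (Sample size section). The margin of error is not stated, so that figure cannot be reproduced. With 50% heterogeneity and alpha 0.05 it implies 1.96 × √(0.25/300) = 5.66%. It serves here only as a scale: 300 for one country, and 14 × 300 = 4,200 pooled. The protocol does not say whether the growth models are fitted by country or pooled, and follow-up is optional with no attrition rate given.

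**Step 1: which safeguard covers which block.** The split is stated for the machine-learning algorithms. The bootstrap and the validation cohort belong to the models run in R and Python. The growth models run in EQS and have none of these.

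**Step 2: candidate paths (assumed).** Six named factors for one outcome give m = 6. Six factors × 3 outcomes give m = 18. The ten predictor rows of Table 1 × 3 outcomes give m = 30. The entry level is assumed to be 0.05, the level used in the Sample size section.

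**Step 3: chance of at least one false path.** With independent tests and no true effects this is 1 − 0.95^m:

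- m = 6: 26.5%, with 6 × 0.05 = 0.3 false paths expected
- m = 18: 60.3%, with 0.9 expected
- m = 30: 78.5%, with 1.5 expected

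**Step 4: what is reported after the search.** A simulation set all true paths to zero and freed the path with the largest Lagrange-multiplier statistic while it exceeded 3.84. It then read the results from the same data and re-evaluated R² in fresh data. There were 1,500 runs per row at N = 300 and 300 runs per row at N = 4,200. It is a one-equation regression stand-in for the structural part of a growth model, and Wald deletion was not simulated. Coefficients and R² are averages over runs in which a path entered.

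| N | m | False path enters | Mean absolute standardized coefficient | R² same data | R² fresh data | Fit test rejects, before → after | Mean RMSEA, before → after |
|---|---|---|---|---|---|---|---|
| 300 | 6 | 25.4% | 0.135 | 0.021 | −0.025 | 5.1% → 0.2% | 0.0157 → 0.0067 |
| 300 | 18 | 60.4% | 0.135 | 0.028 | −0.032 | 6.7% → 0.1% | 0.0149 → 0.0036 |
| 300 | 30 | 77.8% | 0.135 | 0.036 | −0.042 | 8.6% → 0.1% | 0.0145 → 0.0027 |
| 4,200 | 6 | 29.7% | 0.037 | 0.002 | −0.002 | 5.3% → 0.0% | 0.0046 → 0.0016 |
| 4,200 | 18 | 59.0% | 0.036 | 0.002 | −0.002 | 8.0% → 0.0% | 0.0034 → 0.0008 |
| 4,200 | 30 | 82.0% | 0.036 | 0.003 | −0.003 | 6.3% → 0.0% | 0.0033 → 0.0003 |

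How often a false path enters hardly depends on N. How large it looks does: the smallest coefficient that can enter first is about √(3.84/N), which is 0.113 at 300 and 0.030 at 4,200. The fit test, which should reject a correct model about 5% of the time, almost never rejects after the search.

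**Step 5: mean change over time.** A second simulation used a true linear growth model at months 0, 1, 3 and 6 with zero mean change (assumed variances: intercept 15, slope 0.3, residual 9). It freed the best of six residual covariances when chi-square exceeded 3.84. The share of data sets declaring a mean change was the same before and after: 9.6% at N = 300 (250 runs; the excess over 5% was there before the search) and 5.0% at N = 4,200 (200 runs). In modified models the slope moved on average by 0.04 and 0.01 standard errors respectively, and by 0.14 at most.

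**Step 6: effect of a hold-out check.** If a freed path must also reach p < 0.05 in held-out data, the chance of at least one false path is 1 − (1 − 0.05²)^m. That is 1.5%, 4.4% and 7.2% for m = 6, 18 and 30.

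**The case against.** The strongest reply is that the search is limited to changes that follow the study hypotheses, and that most alarming figures ignore this limit. Much of that stands.

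- **Saturation and residual covariances.** A reader might infer that the search soon makes fit perfect. A linear model on four waves has 14 moments and 9 parameters, so five freed parameters use up the 5 degrees of freedom. A search over six residual covariances in a true linear model adds a false one in about 18% of data sets (2,000 runs per N), or 1 − 0.82³ = 45% over three independent outcomes. The protocol does not support this reading. No stated hypothesis concerns residual covariances between waves, and no text says that freeing continues until fit is perfect.
- **Primary objective 1.** A reader might infer that the estimated change in symptoms is compromised. Step 5 shows that it barely moves.
- **Step 3 as the cost of respecification.** It is not. A model fixed in advance with the same null paths tested at 0.05 would share those rates. What the search adds is that the entered paths are selected for being significant and the fit statistics are read after tuning.
- **Risk factors have their own block.** Objective 2 rests on the prediction models, which do have a hold-out and a bootstrap. The growth-model paths are not its only basis.
- **Use of the same data is inferred.** The section names no other data for these models, but the article is condensed and a fuller plan may attach a check.

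What remains is a procedure the protocol does state, bounded by hypotheses given only as examples, with reported statistics that the search makes optimistic.

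**Conclusion.** The point holds in moderate form. Fit of the growth models will tend to be overstated, and chance predictor paths can enter with p-values that are too small and coefficients that are too large. The main risk is to the fit statistics and the associations between predictors and change, not to estimated mean change.

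Size depends on N. Near 300 women per country, or fewer after optional follow-up, a null path that enters shows a standardized coefficient of about 0.135, and R² of 0.021 to 0.036 disappears in fresh data. At the pooled 4,200 the coefficient is about 0.036, R² is 0.002 to 0.003 and the RMSEA shift is about 0.003, which is of little practical weight. The 0.05 entry level, the candidate counts and the independence of tests are assumptions. The documents do not support saying that every model will be distorted.

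**What to change.** In the Data analysis section:

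1. For each outcome, report fit and estimates of the model specified from the hypotheses, before any modification, next to those of the modified model.
2. List every Lagrange-multiplier or Wald change and label it post hoc and exploratory.
3. Choose such changes in the 70% sample already planned. Refit the modified model unchanged in the 30% sample, on pooled data, to check whether its fit and added paths hold.

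The unmodified model need not be the sole main result, since it may fit poorly; showing both lets the reader judge.

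The cost is wording plus one or two extra fits per outcome. Intervals in the 30% check are about 1/√0.3 = 1.8 times as wide as in the full sample. That is the reason to pool: 30% of 4,200 is 1,260 women, whereas 30% of 300 is only 90, before any loss to follow-up.
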